## ***7.3 Drug management***

Drug management should abide by instructions on the drug label and the standard operating procedures for each hospital pharmacy management.

## ***7.4 Procedural method***

It is recommended that the time from randomization to femoral artery puncture should be ≤ 90 minutes. During the procedure, all participants are required to undergo a first

thrombectomy attempt after cerebral angiography evaluation. After the first pass thrombectomy, the operator can determine the remaining procedural plan according to the procedural situation. The operator can use other rescue measures at his/her discretion, including balloon dilatation and/or stenting. The control group could use arterial tirofiban rescue treatment after the first pass of thrombectomy, while intra-arterial tirofiban treatment is not recommended for the study group.

Heparinization during the procedure is prohibited.

### ***7.5 Prohibited drugs in the study***

Avoid using other intravenous drugs that inhibit platelet aggregation within 24 hours after enrollment, such as ginkgo diterpene lactone injection, ginkgo biloba lipid injection, ginkgo biloba “Damo” injection, Ginkgo biloba extract injection, ozagrel sodium injection, Breviscapine injection, Kudiezi Injection, etc.

## **8. Withdrawal and exclusion criteria**

### ***8.1 Withdrawal decided by the investigator***

The investigator can decide to withdraw a patient from the study when the selected participant is not suitable for further study, such as:

- (1) Participants with anaphylaxis or serious adverse events who should stop the study at the investigator’s discretion.
- (2) Deterioration of the participant's symptoms after medication. To protect the participant, the participant will be withdrawn from the study and accept other effective treatments.
- (3) Participant developing new comorbidities, complications, or special physiological changes, which affect the efficacy and safety evaluation.
- (4) If, due to poor compliance, the dosing of drugs is less than 70% or more than 130% of the prescribed dose.

(5) Other reasons indicating it is inappropriate to continue the study.

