**10. Data collection and follow-up**

The study sites are required to collect data on patients at baseline (before randomization); treatment period (day 0; the day of randomization); 24-72 hours after randomization; day 7 (or at discharge if discharged earlier) and 90 days ( $\pm 7$  days) after randomization. All SAEs including death within the 3-month follow-up period are recorded. The assessments at 90-days are to be undertaken by a well-trained investigator, who is blind to treatment allocation, either face to face or by telephone. Source documents, such as patient interview records or questionnaire responses, can be directly entered into the database. Paper case report forms can also be filled in and retained as source documents. Brain imaging will be collected at baseline, during the treatment period, and 24-72 hours ( $\pm 8$  hours). If clinically indicated, patients may receive further brain imaging scans at a later stage. Brain imaging data are collected by each site. The leading site assists each site in uploading image data. After uploading, the leading site is responsible for image analysis.

90-day follow-up is required for all participants in this study. If they die before 90 days, they will be followed up until death. Patients who do not comply with the protocol

and/or terminate the assigned treatment regimen also need to be followed up for 90 days, as their data will be required for the intention-to-treat analysis. The study flow chart lists the types of data and the schedule of evaluation. The leading site will provide the paper version of the case report form and the instruction manual for reference, as well as the guidelines of the case report form and the definition of terms.

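### Section 8.1 lets an unblinded investigator withdraw patients from the study on outcome-related grounds without separating stopping treatment from ending follow-up, which contradicts section 10 and risks selective loss of outcomes

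*Protocol*

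**What the plan says.** Protocol section 8.1 opens permissively: "The investigator can decide to withdraw a patient from the study when the selected participant is not suitable for further study". Its examples are:

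- item (1): "Participants with anaphylaxis or serious adverse events who should stop the study", left to the investigator's judgement;
- item (2), deterioration after medication: "the participant will be withdrawn from the study and accept other effective treatments";
- item (3): new comorbidities or complications that disturb the assessment of efficacy and safety;
- item (4): cases where, through poor compliance, "the dosing of drugs is less than 70% or more than 130% of the prescribed dose";
- item (5): any other reason.

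The section speaks of leaving the study, not of leaving study drug, and is silent on whether imaging, NIHSS and mRS are still collected.

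Section 10 says "90-day follow-up is required for all participants in this study". It adds that patients who fail to comply, or who "terminate the assigned treatment regimen also need to be followed up for 90 days, as their data will be required for the intention-to-treat analysis". Two other places separate drug from follow-up. Section 5.2.3 allows data collection to continue when consent is withdrawn for tirofiban only. The procedure for wrongly included patients in section 6.1 continues endpoint follow-up after the drug is stopped, citing intention to treat.

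**The concern.** The grounds in 8.1 lie very close to the outcomes. Absence of sICH is one of the two conditions of the primary composite (section 9), and sICH within 72 hours is a secondary outcome. A symptomatic bleed would ordinarily show itself as deterioration or be reported as a serious adverse event, which are items (2) and (1). The person deciding knows the allocation: the trial is open-label, and section 6.2 blinds only the central image readers and the 90-day assessor.

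If withdrawal ends data collection, loss of outcome data depends on the outcome. It may also be unequal between arms. Controls have no assigned study drug, so the trigger of worsening after medication and the dosing item bear mainly on tirofiban patients. The primary objective asks for better first-pass recanalization without more sICH. Losing the patients who did badly weakens the second half of that claim, and outcomes that were never collected cannot be recovered at analysis.

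**Working it through.** **The rules side by side**

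| Situation | Section 8.1 | Section 10 |
|---|---|---|
| Deterioration after medication | Leaves the study (worded as a direction) | Followed to day 90 |
| Serious adverse event | May leave the study | Followed to day 90 |
| New complication | May leave the study | Followed to day 90 |
| Poor-compliance dosing | May leave the study | Followed to day 90; non-compliers named explicitly |

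The conflict is sharpest for item (4), which allows withdrawal of the non-compliers that section 10 names as patients to follow. Section 8.2 does not settle it. It asks for follow-up visits after permanent discontinuation only where applicable, and its search for survival status covers patients who withdrew consent, not those withdrawn by the investigator.

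**What can be lost, and when.** First-pass mTICI is read during the procedure and is safe. sICH and 24-72 hour recanalization need later imaging and clinical assessment (section 10.5.1), and mRS needs day 90. Section XI.1 permits carrying the latest observation forward. The flow chart places mRS at baseline, discharge and day 90. If a withdrawn patient has no discharge score, and the baseline score is the pre-stroke one (which exclusion 3 limits to 0-2), a deteriorating patient would be carried forward as doing well.

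**The plan's own figure.** Inputs from section XI.4: 70% versus 50%, two-sided alpha 0.05, power 80%, dropout 7%.

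n = [1.960·√(2·0.6·0.4) + 0.842·√(0.7·0.3 + 0.5·0.5)]² / 0.20² = 93 per arm; 93/0.93 = 100 per arm, 200 in total. The stated size reproduces and the fix does not change it.

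**Illustration of size.** The protocol gives no sICH rates. Assumed: sICH 8% tirofiban, 4% control; first-pass success 55% in both arms, independent of sICH.

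| Pattern | Tirofiban composite | Control composite | Difference (points) |
|---|---|---|---|
| Nothing lost | 0.55×0.92 = 50.6% | 0.55×0.96 = 52.8% | -2.2 |
| Half of tirofiban sICH cases lost | 0.506/0.96 = 52.7% | 52.8% | -0.1 |
| All sICH cases lost, both arms | 0.506/0.92 = 55.0% | 0.528/0.96 = 55.0% | 0.0 |
| All tirofiban sICH cases lost, no control cases | 0.506/0.92 = 55.0% | 52.8% | +2.2 |
| All tirofiban sICH cases kept but recorded as sICH-free | 0.55×1.00 = 55.0% | 52.8% | +2.2 |

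The observed sICH rates would be 0.04/0.96 = 4.2% versus 4% with half of the tirofiban cases lost, and 0% versus 4% with all of them lost.

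**Effect on the test.** Take a true composite rate of 50% in both arms, 100 per arm, and all sICH cases lost in both arms. The apparent rate in an arm is 0.50/(1 - sICH rate). The last column is the upper tail of the two-sided 5% test.

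| Assumed sICH, tirofiban vs control | Apparent difference (points) | Chance of a false result favouring tirofiban (nominal 2.5%) |
|---|---|---|
| 5% vs 5% | 0.0 | 2.5% |
| 8% vs 4% | 54.3 - 52.1 = +2.3 (unrounded rates) | 5.0% |
| 10% vs 5% | 55.6 - 52.6 = +2.9 (unrounded rates) | 5.9% |
| 15% vs 5% | 58.8 - 52.6 = +6.2 | 13.0% |

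The bias therefore does not need one-arm loss. It needs unequal sICH rates or unequal withdrawal.

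**The case against.** The strongest reply is that no section takes these patients out of the analysis. Section 8.3 lists the grounds for exclusion from analysis, and neither deterioration nor a serious adverse event is among them. The full analysis set asks for medication records and an effectiveness evaluation, and first-pass mTICI already supplies the latter. Section 8.2 deletes data only when patient and family refuse to provide any. Section 10 has all serious adverse events over three months recorded, so a hemorrhage that itself prompts withdrawal should already be known. All of this stands. A reader might infer that 8.1 removes sICH cases from the primary and safety outcomes; the text does not support that.

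A reader might also infer that the loss falls on one arm only. Items (1), (3) and (5) apply to both arms, and controls may receive intra-arterial tirofiban as rescue (sections 7.2 and 7.4). An imbalance is plausible but not established.

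A third inference is that item (4) catches infusions stopped early for bleeding. On the section 7.2 regimen the total is 10 + 0.1×1440 = 154 µg/kg, 70% of that is 107.8, and the limit is reached at (107.8 - 10)/6 = 16.3 hours. But item (4) is confined to poor compliance, and a stop decided by the investigator for hemorrhage is not that.

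Finally, the lead sentence of 8.1 is permissive, section 10 is explicit, and the shifts are small against the 20-point design difference. The first two points make the conflict easy to repair but do not remove it, because item (2) is worded as a direction. On the third, a shift of a few points matters little for recanalization but can hide a doubling of sICH.

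Carrying values forward would keep such patients in the denominator, but that is no protection: the last row of the first illustration gives the same +2.2.

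**Conclusion.** The point holds as a contradiction with a risk of bias. Section 8.1 allows withdrawal from the study, and for deterioration directs it, on grounds closely tied to the outcomes, by an investigator who knows the allocation. It does not say that follow-up continues. Section 10 requires that follow-up. What is at risk is data due after withdrawal: sICH not yet ascertained, 24-72 hour recanalization and 90-day mRS.

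The size cannot be fixed from the protocol, which gives neither sICH rates nor expected withdrawals. The move from -2.2 to +2.2 points rests on assumed sICH of 8% versus 4%, 55% first-pass success in both arms independent of sICH, and loss of every tirofiban case and no control case. It is an upper bound for those rates, not a forecast. If sites follow section 10, the loss is nil.

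**What to change.** Reconcile section 8.1 with section 10:

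- State in 8.1 that stopping study treatment for any reason listed there does not end participation.
- Every randomized patient continues to the 24-72 hour imaging and NIHSS and the 90-day mRS, and stays in the full analysis set, unless the patient or surrogate withdraws consent for data collection.
- Leave the decisions on stopping treatment with the investigators, as now. The list in 8.1 need not be deleted; it has to be read as reasons for ending treatment, not follow-up.
- Remove the qualifier in section 8.2 that makes follow-up after discontinuation conditional, so that it agrees with section 10.

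The cost is an amendment of wording and a note to sites. Section 10 already requires these assessments, so there are no new visits, and the sample size stays at 100 per arm.

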## ***8.2 Withdrawal decided by the participant***

According to the informed consent, participants have the right to withdraw from the study at any time. A participant who is lost to follow-up precluding further medication or testing, will also be considered a "withdrawal" (or “drop-off”) although the subject has not explicitly expressed a desire to withdraw from the study.

Patients are free to withdraw from the study at any time (e.g., permanent withdrawal of study drugs and withdrawal from study evaluation), without affecting their further treatment. The withdrawal of informed consent from this study must be confirmed by the investigator and recorded on the patient file and informed consent form. If possible, patients and investigators should re-sign and date the informed consent form. These patients will be asked about the reasons for withdrawal and whether there are adverse events. The reason for permanent discontinuation of the study drug use and the date of the last dose of study drug must be recorded in the patient file.

Patients who permanently discontinued the study drug should receive routine treatment, and if applicable, participate in follow-up visits for the study. If the patient refuses any additional study follow-up and formally withdraws their consent (including whether he/she agrees to continued use of collected clinical data without identity information), the leading center shall be informed at the same time. If the patient and family members refuse to provide any clinical data for the study, the leading center will contact the database to delete all the data of the patient after being notified.

At the end of the originally planned follow-up period of all patients (90 days after randomization), the survival status of patients who withdrew their informed consent will be collected from public sources within the scope allowed by local regulations after their withdrawal of informed consent.

To ensure the validity of the study data, it is important to collect as much data as

possible during the study, especially the survival status (death or survival). Therefore, the investigator should try to collect the survival status information of all patients who withdrew informed consent through public source data at the end of treatment visit and the study closure visit. Participants who withdraw cannot be replaced.

### ***8.3 Criteria of exclusion from data analysis***

Participants who should not be enrolled but have been enrolled, or who have completed the study but have violated some provisions of the study protocol, should be excluded from data analysis according to the investigator, including:

- (1) Those who have not used the prescribed medication.
- (2) Those without any test results after medication.
- (3) Those in whom, due to the use of forbidden drugs, the efficiency and safety cannot be evaluated.

At the blinded review meeting, the principal investigator and statistician will decide whether to eliminate cases and what data set to enter. The reasons for the exclusion should be explained, and their medical notes should be retained for future reference.

## **9. Study outcomes:**

### **Primary outcome:**

A composite primary outcome is defined as first-pass recanalization of targeted vessels without increasing the risk of symptomatic intracranial hemorrhage. "First-pass recanalization" is defined as (1) single pass/use of the device, (2) basic or complete revascularization of the targeted vessels (mTICI  $\geq$  2b) after the first pass, and before other endovascular treatments (stent, balloon dilation, or platelet therapy). If the first DSA angiography before the first attempt of thrombectomy demonstrates mTICI grade  $\geq$  2b, this will also be considered achieving "first-pass recanalization". Symptomatic intracranial hemorrhage was defined according to SITS-MOST criteria.

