#### **V. Study objective**

## **1. Primary objective**

To determine, for acute ischemic stroke patients treated with thrombectomy, whether intravenous tirofiban treatment can increase the probability of first-pass recanalization of targeted vessels without increasing the risk of symptomatic intracranial hemorrhage.

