## **2. General principles**

A superiority test will be conducted in this study. Two-sided  $\alpha=0.05$ , and  $p<0.05$  is considered as a statistical significance threshold. All statistical analyses will be processed with Stata 13.0 or higher statistical software.

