## **4. Primary outcome and sample size estimation**

This study is a 1:1 randomized controlled trial. The study group is the tirofiban combined with thrombectomy group, and the control group is the routine thrombectomy group. The primary outcome of the study is a composite outcome: the probability of first-pass recanalization of targeted vessels without increasing the risk of symptomatic intracranial hemorrhage. The Chi-square test is used to compare the primary endpoint between groups.

According to the retrospective analysis of the International Stroke Perfusion Imaging registry (INSPIRE <https://taste.newcastle.edu.au/key=inspire>) participated in by the research team, the proportion of patients who achieved first-pass recanalization without

symptomatic hemorrhage using intravenous tirofiban before thrombectomy was 71% (94/132), while the rate of patients who achieved first-pass recanalization without symptomatic hemorrhage in direct thrombectomy was 48% (55/115).

The conservative estimate for this project is that the rate of primary outcome will be 70% in the study group and 50% in the control group. With two-sided  $\alpha=0.05$ , power=80%, assuming a 7% dropout rate, the final sample size is 100 subjects in the study group and 100 subjects in the control group, or 200 subjects in total, which was calculated using Stata 13.0 software.

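### The primary outcome is worded as a between-arm comparison of hemorrhage risk, and the one superiority chi-square on the composite cannot establish the no-increase-in-sICH half of the primary objective

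*Protocol*

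**What the plan says.** Section VI.9 of the protocol gives the definition: "A composite primary outcome is defined as first-pass recanalization of targeted vessels without increasing the risk of symptomatic intracranial hemorrhage". It then defines first-pass recanalization in detail (mTICI 2b or better by a stated rule) and refers to the SITS-MOST criteria for sICH, without a time window. Section XI.4 repeats the outcome as "the probability of first-pass recanalization of targeted vessels without increasing the risk of symptomatic intracranial hemorrhage" and adds: "The Chi-square test is used to compare the primary endpoint between groups".

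The same section XI.4 takes its planning rates from a registry, reporting there "the proportion of patients who achieved first-pass recanalization without" symptomatic hemorrhage: 94/132 (71%) with tirofiban and 55/115 (48%) without. From these it plans for 70% against 50%.

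The primary objective (Synopsis and section V.1) is to find out whether tirofiban can "increase the probability of first-pass recanalization of targeted vessels without increasing the risk of symptomatic intracranial hemorrhage". Section XI.2 says: "A superiority test will be conducted in this study". Nowhere does the protocol give an sICH planning rate, a margin or an acceptable upper bound. sICH within 72 hours is listed separately as a secondary outcome in section VI.9.

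**The concern.** There are two linked problems.

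First, a chi-square on a binary endpoint needs a yes or no for each patient. As worded, the second half of the outcome is a property of the comparison between arms and cannot be scored. The sample-size section uses a version that can be scored, so the text carries two wordings of the primary outcome.

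Second, the objective has two parts and the plan has one primary test. Even with a patient-level composite, superiority shows only that more patients were recanalized without sICH. A gain in recanalization can outweigh extra hemorrhages, and an sICH in a patient whose first pass failed changes nothing, because that patient is already a failure. The objective and the outcome use nearly the same words, so a significant composite is easily read as showing that hemorrhage was not increased. That is the safety question on which section IV.3 says previous studies conflict.

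**Working it through.** **Inputs from the protocol (section XI.4):** 70% against 50%, two-sided 0.05, 80% power, 7% dropout, 100 per arm.

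**Assumed inputs:** all sICH rates, because the protocol gives none, and independence of sICH from first-pass recanalization.

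**Step 1. Reproduce the stated sample size** (pooled variance, no continuity correction).
n = [1.96 × √(2 × 0.6 × 0.4) + 0.8416 × √(0.5 × 0.5 + 0.7 × 0.3)]² / 0.20² = (1.3579 + 0.5708)² / 0.04 = 93 per arm. Then 93 / 0.93 = 100 per arm, 200 in total. The figure reproduces. It already rests on the patient-level counts.

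**Step 2. Calibrate first-pass success** so that the composite is exactly 50% and 70% when both arms have the control sICH rate s. Control first-pass success is 0.50/(1 − s) and tirofiban first-pass success is 0.70/(1 − s). At s = 3% these are 51.5% and 72.2%; at 4%, 52.1% and 72.9%; at 5%, 52.6% and 73.7%. Under independence at s = 4%, 1 − 0.521 = 48% of control sICH falls in first-pass failures and has no weight in the composite.

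**Step 3. Raise sICH in the tirofiban arm to t.** Its composite rate becomes 0.70 × (1 − t)/(1 − s). Power = Φ[(d − 1.96 × SE0)/SE1], where d is the difference in rates, SE0 the pooled and SE1 the unpooled standard error.

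Worked case, 3% to 6%, 93 per arm:
- Composite: 0.70 × 0.94/0.97 = 67.8% against 50%. d = 0.1784, SE0 = 0.0722, SE1 = 0.0710, so Φ(0.52) = 70%.
- sICH: 6% against 3%. d = 0.03, SE0 = 0.0304, SE1 = 0.0303, so Φ(−0.98) = 16%.

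| Assumed sICH, control to tirofiban | Composite, control vs tirofiban | Composite power, 93–100 per arm | Power to detect the sICH rise |
|---|---|---|---|
| 3% to 6% | 50% vs 67.8% | 70–73% | 16–17% |
| 3% to 9% | 50% vs 65.7% | 58–61% | 41–43% |
| 4% to 10% | 50% vs 65.6% | 58–61% | 36–38% |
| 5% to 10% | 50% vs 66.3% | 62–65% | 25–27% |

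**Step 4. A more extreme case.** If tirofiban first-pass success were 78% with sICH 10%, and control 52% with sICH 4%, the composite would be 0.78 × 0.90 = 70.2% against 0.52 × 0.96 = 49.9%, with 81% power at 93 per arm. This needs a first-pass benefit beyond the 72.9% that the planned effect implies at 4% sICH.

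**Step 5. A possible data set.** A composite of 70/100 against 50/100 gives chi-square p = 0.004. Those counts are compatible with sICH of 9/100 against 3/100, for which Fisher's exact p = 0.13. A significant primary result and a non-significant sICH test can therefore stand beside a tripled observed rate.

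**Step 6. Precision for sICH.** With identical observed counts in both arms, the Newcombe 95% CI for the difference is ±5.8 points at 3/100, ±6.8 at 5/100 and ±8.0 at 8/100. These widths depend on the assumed counts.

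**The case against.** The intended endpoint can be recovered. A chi-square needs patient-level data, and section XI.4 sets the primary-outcome rate from patient-level registry counts. This stands: the first problem is one of wording, and the sample size is sound. A reader might infer that the trial was planned on a different endpoint or cannot be analysed; the documents do not support that.

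Nor does the protocol state a rule that equates a composite win with no increase in sICH. sICH is a secondary outcome, section XI.3 plans a safety evaluation, and section XIII provides for a monitoring board that sees unblinded data. This also stands. A reader might infer that a false safety conclusion is built into the definition, but how the result will be reported is not fixed. What remains is that the primary objective includes the safety clause, while the stated primary test cannot answer it.

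The composite does penalise hemorrhage. With first-pass success held at the planned effect, its power falls from 80% to between 58% and 70% at 93 per arm. The 81% case needs extra efficacy, so it should not be presented as typical.

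Finally, an analysis plan may specify the sICH comparison and the component tables, so their absence here is not criticised. It would not by itself correct the objective and outcome wording fixed in the protocol.

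**Conclusion.** The point holds in this form: the outcome wording in sections VI.9 and XI.4 cannot be scored per patient, and the superiority chi-square cannot establish the sICH half of the primary objective. Under the assumed doubling to tripling of sICH, with first-pass success calibrated to 70% and 50% at equal sICH, the composite keeps about 58–73% power against about 16–43% for detecting the rise. These sizes rest on assumed sICH rates and on independence. The two structural points need no assumed rate. It would go too far to say that the full planned power survives such a rise, since that requires a first-pass benefit above plan.

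**What to change.** 1. In sections VI.9 and XI.4, define the primary outcome per patient: first-pass mTICI 2b or better by the rule already stated, and no SITS-MOST sICH within 72 hours, the window already used for the secondary outcome.
2. In the Synopsis and section V.1, restate the primary objective as superiority on that composite.
3. State that any conclusion about sICH rests on the separate sICH risk difference with its 95% CI in all randomized patients, and that absence of an increase will not be concluded from a composite win or from a non-significant sICH test.
4. Do not write a fixed excludable margin into the protocol, because any such figure would rest on assumed sICH rates.

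The sample size stays at 100 per arm and no extra data are needed. The cost is a narrower permissible claim and a late amendment: version 3.1 is dated September 2023 and follow-up is scheduled to end in December 2023. The change should be documented as a clarification and made before database lock.

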## ***7.2 Drug dosage and regimen***

**The study group:** intravenous tirofiban combined with thrombectomy. Tirofiban intravenous therapy is initiated within half an hour after randomization and before femoral artery puncture. Tirofiban is used as follows: tirofiban 10 µg/kg, intravenous bolus injection within 3 minutes, and 0.1 µg/kg/min intravenous infusion for 24 hours. The study group is required to maintain tirofiban medication for at least 24 hours according to the protocol. If intracranial hemorrhage is found in follow-up head CT or other serious adverse events (such as gastrointestinal or urinary tract hemorrhage) that may be related to tirofiban within 24 hours, the investigator may consider stopping the medication. The site investigators decide on the subsequent antiplatelet treatment plan based on the patient's condition after 24 hours of intravenous tirofiban infusion.

**The control group:** treated with routine thrombectomy. The control group is not allowed to use intravenous or intraarterial antiplatelet drugs before the first thrombectomy attempt. Other thrombectomy procedures are carried out in accordance with local guidelines. If there is obvious vascular stenosis or re-occlusion after thrombectomy, the operator can use other rescue measures according to the circumstances, including intra-arterial tirofiban treatment. The rescue treatment does not include an intravenous loading dose of tirofiban.

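### Section VI.7.4 requires a first thrombectomy attempt in every participant, with no exemption for vessels that section VI.9 already scores as successes on the first DSA

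*Protocol*

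**What the plan says.** Section VI.9 (Primary outcome) has two numbered conditions for first-pass recanalization: "1) single pass/use of the device, (2) basic or complete revascularization of the targeted vessels", with the grade (mTICI 2b or better) read "after the first pass, and before other endovascular treatments (stent, balloon dilation, or platelet therapy"). It then adds a rule for early reperfusion. "If the first DSA angiography before the first attempt of thrombectomy demonstrates mTICI grade" 2b or better, the patient also counts as having achieved first-pass recanalization.

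Section VI.7.4 (Procedural method) says that "all participants are required to undergo a first" "thrombectomy attempt after cerebral angiography evaluation". No exception is stated. After the first pass, "the operator can determine the remaining procedural plan according to the procedural situation".

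Section VI.8.3 says that participants who completed the study but "have violated some provisions of the study protocol, should be excluded from data analysis according to the investigator". It lists three cases, which concern medication not taken, absence of test results after medication, and forbidden drugs. A blinded review meeting decides on elimination and on the data set. Section XI.1 defines the per-protocol set by completion of the specified treatment or absence of a major violation, and leaves the definition of a major violation to the data review.

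Section VI.7.2 gives the timing of the drug: "Tirofiban intravenous therapy is initiated within half an hour after randomization and before femoral artery puncture".

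**The concern.** The authors foresaw a vessel that is already open on the first angiogram and wrote a scoring rule for it, but the procedural rule was not adjusted to match. The mandatory attempt comes after angiography, which is exactly when the early-reperfusion rule applies. The operator then has two choices.

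- **Comply.** A device is passed in a vessel that already meets the success threshold. The protocol's own background (section IV.1) names endothelial injury, thromboembolic complications and early re-occlusion as risks of arterial intervention.
- **Skip the attempt.** A patient counted as a success now departs from a required step, and the rules on exclusion do not say what follows.

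These patients are not irrelevant to the treatment question. Tirofiban starts before puncture, so reperfusion on the first DSA is one way in which the drug could act. Losing such patients from an analysis set could remove part of the effect that the early-reperfusion rule was written to count.

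**Working it through.** **Is the attempt really mandatory?** Section VI.7.4 describes the 90-minute target from randomization to puncture as recommended, and intra-arterial tirofiban in the study group as not recommended. For the first attempt it uses the language of requirement. Within that section the attempt is an obligation, not advice.

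**Could the drug act before the first DSA?** Section VI.7.2 allows up to 30 minutes from randomization to the start of tirofiban. Section VI.7.4 recommends puncture within 90 minutes of randomization. At those two limits the drug runs for 90 − 30 = 60 minutes before puncture.

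**What happens in each analysis set to a patient who is open on the first DSA and has no device attempt?**

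- *Primary outcome score:* the recanalization component is met under section VI.9, whether or not an attempt follows.
- *Full analysis set (section XI.1):* membership rests on randomization, medication records and an effectiveness evaluation. A device attempt is not a condition.
- *Intention-to-treat follow-up (section VI.10):* patients who do not comply with the protocol are followed for 90 days because their data are needed.
- *Per-protocol set (section XI.1):* depends on whether the data review calls the skipped attempt a major violation. It is not among the examples, but the list is declared open.
- *Section VI.8.3:* the general sentence reaches any violation of some provision, while the listed cases do not include a skipped attempt. Exclusion is therefore possible but not prescribed.

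**Scale in a set from which such patients are removed.** The plan's own figure comes first. With rates 0.70 and 0.50, two-sided α = 0.05, 80% power and pooled variance:

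n = [1.960·√(2·0.6·0.4) + 0.842·√(0.21 + 0.25)]² / 0.20² ≈ 93 per arm

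93/0.93 = 100 per arm, so the stated 200 is reproduced and is not in dispute.

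The protocol gives no rate of reperfusion on the first DSA, so the number k of excluded zero-pass successes is an assumption, taken as 1, 5 or 10 per affected arm. Using 93 per arm for illustration, the rate after exclusion is (93p − k)/(93 − k):

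| k | Study arm (p = 0.70) | Control arm (p = 0.50) | Difference, study arm only excluded | Both arms | Control arm only |
|---|---|---|---|---|---|
| 1 | 64.1/92 = 69.67% | 45.5/92 = 49.46% | 19.67 | 20.22 | 20.54 |
| 5 | 60.1/88 = 68.30% | 41.5/88 = 47.16% | 18.30 | 21.14 | 22.84 |
| 10 | 55.1/83 = 66.39% | 36.5/83 = 43.98% | 16.39 | 22.41 | 26.02 |

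One patient moves the study-arm rate by 0.3 points and the control rate by 0.5 points. The difference shrinks if only study-arm patients are lost. It grows if equal numbers are lost in both arms, or if only control patients are lost.

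**The case against.** The strongest reply is that the two sections do different jobs. Section VI.7.4 gives a sequence, with thrombectomy before balloon, stent or intra-arterial rescue. Section VI.9 gives a score. The words about the first attempt in section VI.9 only time the angiogram and do not say that the attempt is omitted. Both sections can therefore be followed at once, and the score is success either way.

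This stands as far as scoring goes: there is no gap in the primary outcome. It does not remove the procedural problem, because following both sections means a device pass in a vessel already at the success threshold. If section VI.7.4 means only thrombectomy before rescue, it does not say so.

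A second reply is that the main analysis is protected. This also stands. Neither the full analysis set nor the intention-to-treat rule depends on a device attempt, and eliminations are decided at a blinded review. It limits the concern but does not settle the per-protocol set or the broad sentence in section VI.8.3.

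A third reply is that a pass may be clinically sensible, since the threshold takes in basic as well as complete revascularization. That is fair, and it is a reason to lift the requirement without forbidding the attempt.

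A reader might also infer a stronger fault in the outcome definition: that the single-pass condition means one pass in the whole procedure, so that a later pass chosen by an unblinded operator would turn a success into a failure. The text does not support this. The grade is fixed after the first pass, zero-pass patients count as successes, and the number of passes is a separate secondary outcome (section VI.9) and a separate data item (section VI.10.4). Under this natural reading the effect is nil, and clearer wording would be a courtesy, not a correction.

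**Conclusion.** The mismatch is real but modest. Section VI.7.4 obliges an attempt in patients whom section VI.9 already counts as recanalized, and the protocol does not say how a patient in whom it is sensibly omitted should be classified. The main exposure is patient safety, through an unneeded device pass, and the composition of the per-protocol set.

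A reader might go further and conclude that the primary analysis is biased or that these patients will be dropped from it. The documents do not show that. The full analysis set, which is the main efficacy population, has no device-attempt condition, and section VI.8.3 leaves exclusion open without prescribing it.

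The size is unknown. Under the assumed 1, 5 or 10 exclusions, with 93 per arm at the planned rates, the 20.0-point difference becomes 19.7, 18.3 or 16.4 points if only the study arm is affected, and 20.2, 21.1 or 22.4 points if both arms are affected equally. These figures describe scale in a set that excludes such patients, and even the direction depends on how they are spread. The sample size is unaffected.

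**What to change.** Add to section VI.7.4 that patients at mTICI 2b or better on the first DSA are not required to have a thrombectomy attempt, are recorded as having zero passes, are not protocol deviators for that reason, and stay in all analysis sets for which they otherwise qualify. An operator who judges a pass to be clinically indicated may still make one.

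No new patients or data are needed. Section VI.10.4 already records the mTICI grade at first angiography and the number of passes. The cost is one protocol clarification reported by the sites to their ethics committees (section VI.5.1). Version 3.1 is dated September 2023 and follow-up is planned to end in December 2023, so the procedural part helps only patients not yet treated. The analysis-set part remains useful if it is fixed in writing before the blinded review and data lock in section VI.6.3.
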